## **Introduction**

Abdominal surgery is the most common surgery performed worldwide [1]. Elective major abdominal surgery (MAS) is defined as a planned of any abdominal surgery where the total incision length is  $\geq 5$  cm involving open, laparoscopic, or minimally invasive procedures performed under general anaesthesia, with an incision into the abdominal cavity, visceral manipulation, and at least an overnight hospital stay [1].

The most common complication following MAS is a postoperative pulmonary complication (PPCs) with a reported incidence of 13–53 % [2]. Most PPCs manifest within the initial 3 days following surgery [3,4]. Evidence indicates that PPCs are associated with prolonged hospital stays [5,6], an elevated risk of unplanned readmissions [5], diminished quality of life and physical function [7], and an increased risk of all-cause mortality within 12 months [2,5]. Owing to the high incidence of PPCs and their substantial impact on patients, the prediction and targeted prevention of PPCs are strongly recommended [8].

Enhanced Recovery after Surgery (ERAS) is an evidence-based preoperative, intraoperative and postoperative multi-model care pathway that aims to reduce stress response to surgery and accelerate post-op recovery through enhancing patient mobilization, reducing complication rates after surgery, decreasing hospital length of stay and reducing healthcare costs [1,9,10]. Since ERAS was first implemented within hospitals over twenty years ago, post-surgical outcomes have improved for patients [11]. Length of stay has decreased, with no subsequent increase in readmission rates [12], with concurrent improvements in clinical outcomes whilst having a beneficial impact on healthcare resources. ERAS originated in elective colorectal surgery but has spread to other surgical subspecialties, including, but not limited to, gastrointestinal, hepatobiliary, orthopaedic, cardiac, thoracic, head and neck, breast and gynaecologic surgery [13]. The ERAS approach comprises preoperative, intraoperative, and postoperative components, with optimization of the patient's physical status before surgery as a key focus [9]. Therefore, prehabilitation program by physiotherapists is essential in enhancing patients' recovery and improving their outcomes after surgery including physical performances, psychological and health related quality of life [2,14,15].

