## **Literature Review**

Abdominal surgery is the most common surgery performed worldwide. Major abdominal surgery is conducted under general anaesthesia and involves making an incision into the abdominal cavity with manipulation of the internal organs, typically requiring at least an overnight hospital stay (Donati et al., 2004). Physiotherapists studying this population often classify abdominal surgeries based on the size and location of the abdominal incision(s) (Reeve, 2016). Under this definition, major abdominal surgery encompasses gastrointestinal, hepatobiliary, colorectal, urological, vascular, and

gynaecological procedures performed via open or minimally invasive abdominal approaches, but generally excludes laparoscopic surgeries where the total incision length is less than 5 cm

Mounting evidence has firmly established that low levels of cardiorespiratory fitness (CRF) are associated with a high risk of cardiovascular disease, all-cause mortality, and mortality rates attributable to various cancers. Recent studies suggest that in addition to being a strong predictor of cardiovascular and all-cause mortality in both asymptomatic and clinically referred populations, CRF could be especially helpful in the preoperative risk assessment of patients undergoing cardiovascular and noncardiovascular surgery, predicting surgical complications and short-term outcomes in patients subjected to abdominal aortic aneurysm repair, hepatic transplantation, lung cancer resection, upper gastrointestinal surgery, intra-abdominal surgery, bariatric surgery, and coronary artery bypass grafting. In addition, when patients with coronary artery disease who had to wait in the hospital for coronary artery bypass grafting were randomized into an exercise training group, outcomes were superior to those in the standard care group, because of a reduced rate of postoperative complications and shorter hospital stays were observed (Ross 2016)

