### **Study population**

#### **Inclusion criteria**

- Adults aged 18 and above.
- Scheduled for major abdominal surgery.
- Able to perform the Six-Minute Walk Test (6MWT).
- Provide written informed consent.

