## **Blinding and allocation**

Patients and outcome assessors, will remain blinded to treatment allocation. However, the treating physiotherapists cannot be blinded due to the nature of the intervention. To maintain blinding, details of the intervention will not be recorded in the medical records. Outcome assessments will be conducted by a blinded assessor based off-site from the outpatient department, ensuring impartiality in both inpatient and outpatient settings. Intervention sessions will occur on different days from those scheduled for outcome assessments to further reduce the risk of unblinding. If a participant from the intervention group discloses details of their intervention to the assessor, this will be documented and reported, with the rationale recorded. All analyses will be performed on an intention-to-treat basis once randomization is unblinded.

Following recruitment and baseline assessments, participants will be randomly assigned to one of two groups which will be control group (MICT) or the intervention group (HIIT) using a computer-generated random number sequence. Allocation will be conducted by an independent individual utilizing a block randomization method (5 blocks of 14). An administrative assistant, independent of the trial, will prepare 70 sequentially numbered opaque envelopes, each containing a group allocation. A physiotherapist, trained in the study protocol, will deliver the intervention. Participants in the control group will receive moderate-intensity continuous training (MICT), while those in the intervention group will engage in high-intensity interval training (HIIT) preoperatively. Both groups will commence and conclude sessions with a warm-up and cool down to mitigate the risk of adverse events.

This study is will be conducted at a teaching hospital of the Hospital Canselor Tuanku Muhriz, Malaysia. Prospective consecutive patients will be invited to participate in the study prior to elective major abdominal surgery from February 2025 to July 2026. Fig 2 summarises the design of the trial, and each of the trial's aspect is described in detail below.

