## Data collection

Demographic data and preoperative, intraoperative, and postoperative variables will be collected from participants and their medical records. Baseline assessments will be conducted 4 ( $\pm 1$ ) weeks in outpatient setting following referral for exercise based prehabilitation prior to date of surgery. Follow up assessment will continue to 2 days ( $\pm 1$ ) before operation in the inpatient setting, prior to discharge, 4 -weeks, and 12-week post operatively. These follow-ups will take place in the research room within the physiotherapy unit.

All measurements will be conducted by an independent, trained assessor located off-site, who will remain blinded to group allocation. Face-to-face administration of follow-up tests and questionnaires will be performed by outcome assessors at four time points: preoperatively, prior to discharge, 4 weeks, and 3 months postoperatively, to maintain consistency across participants.

Post-hospital discharge follow-ups will be contacted via phone. Participants who cannot be reached by phone for 14 consecutive days from the scheduled assessment date will be considered lost to follow-up for post-discharge outcomes.

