## Statistical analysis

The analysis will follow the intention-to-treat, whereby all participants will be analyzed according to the groups to which they were originally randomized, regardless of their adherence to the intervention protocol. SPSS version 27.0 will be used to analyse all collected data. Missing data will be handled using multiple imputation, which creates several datasets by statistically estimating missing values and then combines the results to account for uncertainty. This method is preferred over last observation carried forward, as it reduces bias and more accurately reflects variability in clinical studies [61].

Descriptive statistics will summarize participants' baseline demographic and clinical characteristics. Continuous variables will be reported as mean (standard deviation, SD) or median (interquartile range, IQR) depending on the distribution, while categorical variables will be reported as frequency (percentage). Baseline comparability analysis of the clinical outcomes between groups will be performed using independent *t*-tests for continuous variables and Chi-square tests for categorical variables.

The primary outcomes (6MWT and MIP) and secondary outcomes (1MSTS, SPPB, hand grip strength, FSS, Bio-impedance Test, EuroQol, SAQ and Global Rating of Change Scale) will be measured at multiple time points: baseline, post-prehabilitation (4 weeks), before hospital discharge, and at 4 and 12 weeks postoperatively. To evaluate changes over time and between-group differences, a linear mixed-effects model (mixed model ANOVA) will be employed, provided the assumptions of normality and sphericity are met. Normality will be evaluated using the Kolmogorov–Smirnov test, while sphericity will be assessed using Mauchly's test. Mixed model ANOVA will provide results for time effect, group effect, and time-group interaction effect. Statistically significant time effect and group effect indicates significant within-group changes and between-group difference respectively, while significant time-group interaction effect determine if the interventions yield the desired effect on the dependent variables. Post hoc pairwise comparisons will be conducted using Bonferroni correction where appropriate.

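### The stated outcome model has no term for surgical approach, so three of the four follow-up comparisons carry variance that a term for the booked approach could remove; the loss is modest and affects precision only

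*Protocol*

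**What the plan says.** - **Visits.** The Protocol, Statistical analysis, measures the outcomes at "baseline, post-prehabilitation (4 weeks), before hospital discharge, and at 4 and 12 weeks postoperatively". Of the four follow-ups, one precedes surgery and three follow it.
- **Operations admitted.** The inclusion criterion is "Scheduled for major abdominal surgery", with no limit by specialty or approach. The Introduction defines such surgery as "involving open, laparoscopic, or minimally invasive procedures performed under general anaesthesia", with a total incision of at least 5 cm. The Literature Review names six specialties, the last being "gynaecological procedures performed via open or minimally invasive abdominal approaches".
- **Allocation.** Under Blinding and allocation, patients are randomised in five blocks of 14. No stratification factor is named.
- **Model.** Under Statistical analysis: "Mixed model ANOVA will provide results for time effect, group effect, and time-group interaction effect". The interaction is the test said to show whether the interventions had the desired effect. No covariate is named.
- **Data.** Under Data collection: "Demographic data and preoperative, intraoperative, and postoperative variables will be collected from participants and their medical records". The only analysis given perioperative factors is an exploratory logistic regression for respiratory complications. Age and gender are baseline items in the schedule of assessments.

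**The concern.** How far a patient walks at discharge, or 4 or 12 weeks after surgery, plausibly depends on whether the operation was open or minimally invasive. A stable patient characteristic is largely absorbed in a repeated-measures model, because each patient also has a baseline value. The effect of the operation is different: it is absent at baseline and before surgery and appears only afterwards. It is therefore an approach-by-time effect, and a model with only time, group and their interaction leaves it in the error of the postoperative comparisons and of the interaction test.

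At stake is the width of the postoperative confidence intervals in a trial with little precision to spare. The preoperative visit is unaffected.

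**Working it through.** **Inputs from the Protocol (Sampling and Size Calculation).** Planning difference 29.4 m, SD 101.6 m, 54 evaluable patients, 70 recruited, 35 per arm. The two-sided 5% level is in Statistical analysis.

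**Assumptions, not in the documents.** Difference D between open and minimally invasive patients after surgery: 40-80 m. Share p booked for open surgery: 0.3-0.5. The SD of 101.6 m is taken to apply at a postoperative visit.

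**1. The plan's own figure.** 29.4/101.6 = 0.29, as stated. The stated requirement of 54 does not follow: a two-sided two-sample comparison at 80% power needs 188 per arm (376 in all). With 35 per arm the standard error at one visit is 101.6 × √(2/35) = 24.3 m, and power for 29.4 m is Φ(29.4/24.3 − 1.96) = 22.7%. The sample size is a separate matter; it is the background here.

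**2. Variance explained by approach.** R² = p(1 − p)D²/SD², with SD² = 10,322.6. Equivalent number of patients = 70/(1 − R²). Standard error = 24.3 × √(1 − R²) m.

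| p | D (m) | R² | Equivalent patients | Standard error (m) | Power for 29.4 m |
|---|---|---|---|---|---|
| 0.3 | 40 | 336/10,322.6 = 0.033 | 72 | 23.9 | 23.3% |
| 0.3 | 80 | 1,344/10,322.6 = 0.130 | 80 | 22.6 | 25.4% |
| 0.5 | 40 | 400/10,322.6 = 0.039 | 73 | 23.8 | 23.4% |
| 0.5 | 60 | 900/10,322.6 = 0.087 | 77 | 23.2 | 24.4% |
| 0.5 | 80 | 1,600/10,322.6 = 0.155 | 83 | 22.3 | 26.0% |

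Approach explains about 3-16% of the variance, and adjusting for it is worth about 72-83 patients instead of 70.

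**3. Chance imbalance is the same quantity.** With p = 0.5, the between-arm difference in the open share has SD √(2 × 0.25/35) = 0.12, which moves the comparison by 4.8-9.6 m at one SD. Squared and divided by the squared standard error of 24.3 m, this gives 0.039-0.155, exactly R² in step 2. The imbalance is already inside the unadjusted confidence interval and must not be added to the loss of precision.

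**4. Price of adjustment.** With k covariates at one visit and N evaluable patients, the expected variance inflates by (N − 3)/(N − 3 − k). With N = 54:

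- Approach alone: 51/50 = 1.02. It breaks even at R² = 1 − 50/51 = 2.0%, below the assumed range. The net variance is 0.967 × 1.02 = 0.99 to 0.845 × 1.02 = 0.86 of the unadjusted value.
- Approach, age and sex, all charged at one visit: 51/48 = 1.06, breaking even at 5.9%.
- Approach, operation group, age and sex: 51/47 = 1.085, breaking even at 7.8%, so the lower part of the 3-16% range would bring no gain unless the other terms also explained variance.

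This is why the adjustment should stay small.

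**The case against.** **Covariates can be left to the statistical analysis plan, and an unadjusted analysis of a randomised trial is valid.** Both statements are true, and nothing in the Protocol forbids covariates. But the Protocol does state which effects its model yields, and its contents page lists a statistical analysis plan as its own section 2.8. The point is therefore a stated method with a better alternative. It is not an error of validity.

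**The decisive inputs are assumed.** This stands. The documents give neither the effect of approach nor the share of open operations. The six-specialty list is a general definition in the Literature Review, and the real mix at this one hospital is unknown. It is also an inference from patients being scheduled that the approach is known before randomisation.

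**The gain is small.** This stands too: within the assumed range, power moves from 22.7% to at most 26.0%.

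**Stronger readings that the documents do not support.** A reader might infer that the unstratified design biases the result. It does not: randomisation keeps the unadjusted comparison unbiased in expectation. A reader might also work out that imbalance could shift the result by 10-19 m, or 33-65% of 29.4 m. That needs an imbalance of two SDs (24 percentage points), a tail event, and it restates the variance loss. Nor does the concern call for stratified allocation: six specialties by two approaches would make 12 strata, unworkable with 70 patients in blocks of 14.

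**Conclusion.** The point holds as a modest, cheap gain in precision. The stated model leaves operation-related variance in three of the four follow-up comparisons, and the baseline value cannot remove the part that arises at surgery. Under the assumed 40-80 m difference and 30-50% open share, that is about 3-16% of the 6-minute walk variance, or about 72-83 patients' worth of information from 70. The size depends entirely on those assumptions and on using 101.6 m as the postoperative SD. If the comparison is of change from baseline and the baseline-to-follow-up correlation were 0.7 (also assumed), the change SD would be 101.6 × √(2 × 0.3) = 79 m and the range at half open would be 6-26%; at correlation 0.5 it is unchanged. No bias is shown, the allocation method is not at fault, and adjustment would not rescue the trial's power.

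**What to change.** In the Protocol, Statistical analysis, prespecify before unblinding:

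- the booked approach (open or minimally invasive), recorded before randomisation, as a fixed effect with a by-visit term;
- age and sex as main effects only.

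Use the approach as booked, never the operation performed, so that the model conditions on nothing that happens after randomisation. Leave the allocation scheme as it is. Do not add operation group or further by-visit terms, because the sample cannot pay for them.

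The cost is one extra baseline field, since the patient form in the appendix shows none for the booked procedure, and a few degrees of freedom: about 2% variance inflation for the approach term at one visit with 54 evaluable patients. Age and sex are already collected. As main effects they do little for the time-by-group test, where stable differences in level already cancel.

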## **1.3. Objectives**

### **Primary Objective**

To determine the effect of HIIT over MICT on physical performance which is cardiorespiratory fitness (6MWT) and maximum inspiratory pressure among patients undergoing major abdominal surgery.

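### The primary analysis averages the pre-randomisation baseline into the group effect and lets a non-directional 4-df interaction decide, with no primary visit or contrast fixed and a sphericity condition that has no fallback

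*Protocol*

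**What the plan says.** The Primary Objective names two outcomes, "which is cardiorespiratory fitness (6MWT) and maximum inspiratory pressure among patients undergoing major abdominal surgery". The Phase 2 Statistical analysis section says that the primary and secondary outcomes "will be measured at multiple time points: baseline, post-prehabilitation (4 weeks), before hospital discharge, and at 4 and 12 weeks postoperatively". For all of them, "a linear mixed-effects model (mixed model ANOVA) will be employed, provided the assumptions of normality and sphericity are met". The check is that "sphericity will be assessed using Mauchly's test", with a Kolmogorov–Smirnov test for normality. No correction or alternative model is named if either check fails.

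The section then fixes how the results are read: "Statistically significant time effect and group effect indicates significant within-group changes and between-group difference respectively", while a "significant time-group interaction effect determine if the interventions yield the desired effect on the dependent variables". Bonferroni pairwise comparisons, Cohen's d and mean differences with 95% CI are also planned, but none is named as primary. The assessment schedule (Fig. 1) lists both primary outcomes at all five visits and singles out none.

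Three other places bear on this. Blinding and allocation says that randomisation follows the baseline assessments. The Introduction and section 1.4 state the hypothesis as non-inferiority of HIIT to MICT; the Introduction refers to a margin, but the protocol gives no value for it. The Abstract mentions the mixed ANOVA for the secondary outcomes only, whereas the Statistical analysis section applies it to the primary outcomes as well.

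**The concern.** These are stated decision rules, not details left open for a statistical analysis plan, and they do not answer the trial's question.

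- **Group effect.** Baseline is one of five levels averaged into the quantity read as the between-group difference. Randomisation makes the expected baseline difference zero, so including it shrinks the estimate.
- **Interaction.** It tests whether the two profiles over time are parallel. It becomes significant for any departure, including HIIT recovering worse. Non-inferiority needs a directional estimate with a confidence limit, which this p-value does not provide.
- **No primary visit or contrast.** Neither p-value maps to a difference in metres (or in MIP units) at a stated time.
- **Sphericity condition.** A linear mixed model with unstructured covariance does not need sphericity; a repeated-measures ANOVA does. The text treats the two as one. If Mauchly's test rejects, no analysis is specified.

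At stake is whether the primary result is pre-specified, and whether the number reported as the treatment difference is the treatment difference.

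**Working it through.** **Inputs.** From Sampling and Size Calculation: difference 29.4 m, SD 101.6 m, 35 per arm. The stated effect size reproduces: 29.4/101.6 = 0.289, or 0.29. From Statistical analysis: five time points, two-sided 5%. Not in the documents and therefore assumed: the correlation between visits (r = 0.5 to 0.7, equal for all pairs in steps 1 to 3) and the pattern of the effect over time. The stated sample size of 54 is a separate matter and nothing here depends on it.

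**1. Dilution of the group effect.** The group effect targets the mean of the five visit differences.

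- Constant effect (0, 29.4, 29.4, 29.4, 29.4): 4/5 × 29.4 = 23.5 m.
- Fading effect (0, 100%, 75%, 50%, 25%): 2.5/5 × 29.4 = 14.7 m.
- Pre-operative only (0, 29.4, 0, 0, 0): 1/5 × 29.4 = 5.9 m.

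This step needs no covariance assumption.

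**2. The interaction has no direction.** Its degrees of freedom are (2−1)(5−1) = 4. Under equal correlations its noncentrality is λ = (n/2) Σ(Dⱼ − D̄)²/(1 − r), with n = 35 per arm and differences D in SD units.

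- Sustained benefit (0, d, d, d, d): Σ = 0.8d².
- Sustained harm (0, −d, −d, −d, −d): Σ = 0.8d².
- Pre-operative benefit only (0, d, 0, 0, 0): Σ = 0.8d².

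All three give the same λ and so the same chance of significance. One p-value cannot tell them apart.

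**3. Power for a sustained d = 0.29, 70 analysed.** With n/2 = 17.5 and d² = 0.0841:

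| Test | λ | r = 0.5 | r = 0.7 |
|---|---|---|---|
| Group effect | 17.5 × (0.8d)² / [(1+4r)/5] | 1.57 → 24% | 1.24 → 20% |
| Interaction, 4 df | 17.5 × 0.8d² / (1−r) | 2.35 → 19% | 3.92 → 31% |
| Baseline-adjusted, one visit | 17.5 × d² / (1−r²) | 1.96 → 28% | 2.89 → 39% |
| Baseline-adjusted, mean of four later visits | 17.5 × d² / [(1+3r)/4 − r²] | 3.92 → 50% | 5.16 → 61% |

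These are powers to detect a difference. They compare the sensitivity of the tests; power for non-inferiority would depend on the margin.

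**4. Will the sphericity check fail?** Simulation, 4,000 trials per case, 27 and 35 per arm:

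| Assumed covariance | Mauchly rejects (27 / 35 per arm) |
|---|---|
| Equal correlations 0.6, equal SDs | 5.5% / 4.8% |
| Same, discharge SD 1.15 times larger | 8% / 11% |
| Same, discharge SD 1.3 times larger | 30% / 39% |
| Correlation decaying with time (three versions) | about 100% / 100% |

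In the decaying cases the uncorrected interaction test had a false-positive rate of about 6–7% instead of 5%.

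**The case against.** The strongest defence is that the section gives each test its own role and also promises mean differences with 95% CI, effect sizes and Bonferroni comparisons. Direction and size would therefore be visible in the report. That softens the defect. It does not remove it, because no visit or contrast is designated and a reader could not tell which of several differences was the planned one.

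Three stronger readings are tempting and not supported.

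- **That sphericity will fail.** Surgery falls between the second and third visits and the visits are unevenly spaced, so failure is likely. But the documents give no covariance, and the rejection rate runs from about 5% to about 100% by assumption. The power figures above assume a covariance under which sphericity holds, so they and the high rejection rates do not describe the same trial.
- **That either test counts as success, giving up to 1 − 0.95² = 9.75% false positives.** The text gives the decision to the interaction, so this is not the error rate of the stated rule. For the same reason the dilution affects the reported between-group difference, not the deciding test.
- **That the pre-operative visit must be primary.** The Introduction's hypothesis concerns outcomes following surgery, and the literature review ends by asking about effects after the operation. If the effect is sustained, the mean of the later visits is also the more powerful choice. The investigators should decide.

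It is also fair to say that every option is underpowered at d = 0.29. Better analysis helps but does not cure that.

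**Conclusion.** The point holds. Two conclusions are certain from the text and arithmetic alone: the group effect retains only four fifths of a constant effect (23.5 of 29.4 m) and less of a fading one, and the interaction cannot show benefit or non-inferiority because it is blind to direction. It is also plain that no primary visit or contrast is fixed and that the analysis is conditional on checks with no stated alternative.

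The size of the power loss rests on the assumed r of 0.5 to 0.7, equal correlations, a sustained effect and all 70 patients analysed. Under those assumptions the planned tests reach 19–31%, against 28–39% for a baseline-adjusted single visit and 50–61% for the baseline-adjusted mean of the later visits. That sphericity fails is likely, not established. The case for change does not need it, because a conditional analysis without a fallback is not pre-specified either way.

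**What to change.** For both 6MWT and MIP, replace the rule with a linear mixed model on the four post-baseline values: fixed effects for group, visit, group-by-visit, baseline value and baseline-by-visit, with unstructured within-patient covariance.

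Before unblinding, the investigators name one primary contrast: either a single visit (for example the end of prehabilitation) or the mean of the later visits. They report the adjusted HIIT–MICT difference with its 95% CI and read it against the non-inferiority margin to which the Introduction refers. The remaining visits become secondary contrasts from the same model.

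Delete the Mauchly and Kolmogorov–Smirnov conditions and the sentence that gives the decision to the interaction p-value. Align the Abstract, which ties the mixed ANOVA to the secondary outcomes only.

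Cost: a protocol amendment, which the ethics approval letter requires to be approved, and a few more model parameters. No new data are needed, because the schedule already has both outcomes at every visit. Data collection is planned to conclude in October 2026, so the amendment should be in place before then.
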